#### Data analysis

Analysis of data will be based on the intention-to-treat principle. I.e., all patients randomized will be included in the analysis regardless of adherence to the allocated intervention. The primary outcome and other continuous outcomes will be analysed using a repeated measurement, likelihood-based, mixed-effects model with an unstructured covariance matrix. This analysis will include measurement at baseline and 12 months for the primary outcome, and all measurements (baseline, 12 months, and 24 months post-intervention) for the follow-up results, and is an appropriate approach to handling missing data. Dichotomous outcomes will be analysed using logistic regression. In case more than 5% of data is missing at follow up we will use multiple imputation to handle missing data. The imputations will be based on a linear regression model with 100 imputations and 20 iterations. The pooled analysis will subsequently be used for our analysis.

All statistical analysis will be conducted in SPSS. All tests will be two-tailed and unless otherwise mentioned the alpha level will be set at 0.01666.

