### Patient inclusion criteria

1) Adults,  $\geq 18$  years, fulfilling the ICD-10 diagnostic criteria for schizophrenia, persistent delusional disorders, or schizoaffective disorders [35] using the Schedule for Clinical Assessment in Neuropsychiatry (SCAN) [36]; 2) Waist circumference  $\geq 88$  cm for females and  $\geq 102$  cm for males [37] measured between the crista iliac and lowest rib; and 3) Written informed consent.

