### Randomization and blinding

Patients were randomized with a 1:1:1 ratio to either the lifestyle coaching versus care coordination versus treatment as usual. Randomization was stratified according to the two psychiatric centres, sex, and a high/low risk of cardiovascular disease. High risk was defined according to cut-off points from a Danish population study using the Copenhagen risk score, aiming to identify the quintile at highest risk. Each person was – in the computer program – simulated as 60 years old, to reach a substantial level of risk [38]. This approach is was recommended by the

European cardiovascular risk factor management guidelines to assess risk in young individuals [39].

The randomization was centralized and carried out by the Copenhagen Trial Unit using a computerized randomization sequence with alternating block sizes unknown to the investigators. After inclusion in the trial, a health care provider contacted the Copenhagen Trial Unit with a unique patient identifier plus stratification variables and in return received the patient allocation.

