### Exploratory outcomes

Anthropometric measures: weight in kg and body mass index, skinfolds measured at four sites (biceps, triceps, subscapular, suprailiac), and body fat percentage calculated from skinfold measures [50].

Psychometric measures: positive and negative symptoms (SAPS and SANS) [51], cognition (BACS) [52], quality of life (MANSA and EQ-5D) [53], global assessment of functioning (GAF) [54], perceived health [55], and perceived stress [56].

Biomedical status measures: triglycerides, high sensitive CRP (hsCRP), low-density lipoprotein cholesterol (LDL).

Lifestyle measures: food frequency questionnaire [57], 24 hour recall, self-reported point abstinence from smoking (nicotine dependence questionnaire [58]).

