### Strengths and limitations

The CHANGE trial has several strengths. First, the design has central randomization, blinded outcome assessments, data management, data analysis, and independent funding [73-79]. Second, we planned our sample size to avoid substantial type 2 errors. Third, we use a manual-based, well described, and evidence-based theoretical framework. Fourth, the approach has a high intensity intervention, offering an assertive approach with at least weekly personal contact. Fifth, we have a multifaceted method, allowing the staff to work on all the known risk factors. Sixth, our composite outcome integrates the results even though they might be heterogeneous. Seventh, by comparing care-coordination with the lifestyle coaching, we will be able to differentiate between the effect of sufficient monitoring and treatment of somatic comorbidity and the effect of lifestyle changes, so a significant difference between the two intervention groups will point at an add-on effect of lifestyle coaching. Eighth, all contacts, and the focus of the contact, with patients are registered. Ninth, the intervention is developed to be sustainable, using low-budget possibilities in the neighbourhood to enable the patients to create long lasting changes. Ninth, we will be able to follow patients through Danish publish register to assess any long-term effects [80].

There are also limitations. Regarding some of the secondary outcomes, we will not have power to detect a clinically relevant difference, for example smoking cessation, why this important outcome has been categorized as an exploratory outcome. The thorough examination at baseline might initialize some lifestyle changes in patients randomized to the control group. The external validity is directed by the selection of patients with abdominal obesity; hence our results will only be valid for this group of patients. Moreover, an unavoidably limitation is also the selection bias created by a heightened motivation to change lifestyle habits, just by accepting participation in the CHANGE trial. Choosing a surrogate outcome like the Copenhagen risk score is a limitation due to the risk scores possible inaccuracy in predicting actual morbidity and mortality [81]. Furthermore, even though an individualized approach is necessary in order to implement lifestyle changes in daily life, it makes the trial vulnerable regarding its external validity, as not all patients will have the same interventions.

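### Smoking abstinence, an exploratory outcome, falls under a logistic-regression rule for all randomised patients with no stated baseline smoking term; taken literally, this dilutes a cessation effect

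*Protocol*

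**What the plan says.** The protocol's Data analysis section adopts intention to treat, so that "all patients randomized will be included in the analysis regardless of adherence to the allocated intervention". For binary endpoints it adds one sentence: "Dichotomous outcomes will be analysed using logistic regression". For the primary and other continuous outcomes the baseline measurement enters the repeated-measures model. No counterpart is given for binary outcomes. No covariate is named or ruled out for any model.

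Exploratory outcomes lists "self-reported point abstinence from smoking" among the lifestyle measures, with no denominator. It is the one listed outcome that is plainly dichotomous. Strengths and limitations refers to it as "smoking cessation, why this important outcome has been categorized as an exploratory outcome", the stated reason being lack of power.

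The inclusion criteria are diagnosis ("fulfilling the ICD-10 diagnostic criteria for schizophrenia, persistent delusional disorders, or schizoaffective disorders"), a waist threshold and consent. The exclusions are pregnancy and inability to consent. Smokers and non-smokers can both enter.

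**The concern.** Only a smoker can quit. If abstinence is scored in everyone, a patient who did not smoke at entry is normally abstinent at 12 and 24 months whatever the arm. The comparison then concerns the prevalence of non-smoking, while the protocol discusses the outcome as cessation.

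Smoking is one of the three behaviours that coaching targets, and it is an input to the Copenhagen risk score. A real effect among smokers would appear as a much smaller odds ratio with a wider relative margin of error, and the smoking component could look weaker than it was. Lack of power is openly accepted for this outcome, but part of the shortfall under this rule would come from the choice of denominator and model.

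**Working it through.** **The plan's own figure.** The protocol has no calculation for smoking. Its sample size for the primary outcome (difference 2.5, SD 5.9, alpha 0.0166 two-sided, power 90%) reproduces:

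n = 2 × 5.9² × (2.395 + 1.282)² / 2.5² = 150.6, so 151 per arm against the stated 150. Power at 150 is 0.899. I therefore use 150 per arm and two-sided alpha 0.05/3.

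**Inputs.**
- From the protocol: 150 per arm (Sample size), and alpha 0.01666 with two-tailed tests (Data analysis).
- Assumed, because the protocol gives no figures: smoker share at baseline s = 40-80%; abstinence among baseline smokers q of 5% v 15%, 5% v 20% or 10% v 20%; no uptake among baseline non-smokers.

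**Formulas.** All randomised: P = (1 − s) + s × q in each arm, n = 150. Smokers only: P = q, n = 150 × s. The all-randomised risk difference is therefore s × (q1 − q0).

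Power = Φ[(d − z × SE0) / SE1], with z = 2.394, SE0 from the pooled proportion and SE1 from the separate proportions.

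**One case in full (s = 0.5, 5% v 20%).**
- All randomised: P0 = 0.5 + 0.5 × 0.05 = 0.525 and P1 = 0.5 + 0.5 × 0.20 = 0.600. OR = (0.600/0.400) / (0.525/0.475) = 1.36. SE0 = 0.0573, SE1 = 0.0571. (0.075 − 2.394 × 0.0573) / 0.0571 = −1.09, so power is 0.14.
- Smokers only, 75 per arm: OR = (0.20/0.80) / (0.05/0.95) = 4.75. SE0 = 0.0540, SE1 = 0.0526. (0.15 − 2.394 × 0.0540) / 0.0526 = 0.39, so power is 0.65.

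**Range.**

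| Abstinence among smokers | Smoker share | Risk difference, all randomised | OR, all randomised | Power, all randomised | OR, smokers only | Power, smokers only |
|---|---|---|---|---|---|---|
| 5% v 15% | 40% | 4 points | 1.19 | 0.05 | 3.35 | 0.28 |
| 5% v 15% | 50% | 5 points | 1.22 | 0.06 | 3.35 | 0.36 |
| 5% v 15% | 80% | 8 points | 1.49 | 0.20 | 3.35 | 0.58 |
| 5% v 20% | 40% | 6 points | 1.30 | 0.10 | 4.75 | 0.54 |
| 5% v 20% | 50% | 7.5 points | 1.36 | 0.14 | 4.75 | 0.65 |
| 5% v 20% | 80% | 12 points | 1.78 | 0.45 | 4.75 | 0.87 |
| 10% v 20% | 40% | 4 points | 1.20 | 0.05 | 2.25 | 0.19 |
| 10% v 20% | 80% | 8 points | 1.45 | 0.18 | 2.25 | 0.41 |

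If 5% of baseline non-smokers are smoking at follow-up, all-randomised power changes by about 0.01 at most.

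**Does a baseline term recover the loss?** Two simulations at 50% smokers:
- 5% v 15%, 2% uptake among non-smokers, 1,500 runs: unadjusted OR 1.24, power 0.07; with a baseline smoking term OR 2.71, power 0.21; smokers only OR 3.40, power 0.23.
- 5% v 20%, 3% uptake: power 0.14, 0.48 and 0.56 respectively.

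Most of the loss is recovered either way. The simulated smokers-only powers (0.23 and 0.56) lie below the formula values (0.36 and 0.65), so the formula is somewhat optimistic for the small subset. The ordering does not change.

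**The case against.** The strongest reply is that this reads silence as a decision. A reader might infer that the protocol has chosen to leave baseline smoking out of the model. It has not: covariates are discussed for no model, and covariates and denominators of an exploratory outcome are often left to a statistical analysis plan, which is not at hand. The word cessation, and the link to a nicotine dependence questionnaire, also fit a smokers-only denominator. The intention-to-treat sentence is aimed at exclusions for non-adherence. All of that stands. What remains is that the analysis set is stated, and no exception is made for the one outcome that only smokers can achieve.

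Three further inferences are tempting and not supported:
- **The effect is diluted almost to nothing.** With 40-80% smokers, 40-80% of the risk difference remains. Only the odds ratio comes near 1, mainly at the lower smoker shares.
- **Chance imbalance in baseline smoking is an added harm.** Under simple randomisation with 50% smokers its standard error is √(2 × 0.25/150) = 5.8 points. But "Randomization was stratified according to the two psychiatric centres, sex, and a high/low risk of cardiovascular disease", and smoking is an input to that risk score, so smoking is partly balanced. This variation is also already within the outcome's sampling error (5.7 points in the worked case).
- **The low-power remark is wrong.** The protocol says "Regarding some of the secondary outcomes, we will not have power to detect a clinically relevant difference, for example smoking cessation". Among smokers only, power for a 10-point effect is still 0.19-0.58 over the assumed range. The remark does not say which denominator it used, and it mostly holds after the change.

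**Conclusion.** The point holds as a limited one. The stated rule, followed literally, puts baseline non-smokers among the abstinent in every arm. It multiplies the risk difference by the smoker share and cuts power severalfold in most of the cases examined. The direction follows from the text and the arithmetic. The size rests on assumed smoker shares and quit rates, since the protocol gives neither.

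The consequence is confined to an exploratory outcome that is already declared underpowered. The primary analysis, which uses the baseline measurement, is not affected. The change is worth making because it uses a baseline value already collected and costs almost nothing.

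**What to change.** In Exploratory outcomes and Data analysis, state one of two options:

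1. Abstinence at 12 and 24 months is analysed by logistic regression among patients who smoked at baseline. Smoking status feeds the risk score used for stratification, so it is known before randomisation and the subset keeps the randomised comparison.
2. All randomised patients are kept and baseline smoking status is included as a covariate. This model assumes a common odds ratio in smokers and non-smokers. If no baseline non-smoker takes up smoking, the smoking coefficient cannot be estimated, and the arm effect then comes from the smokers alone.

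The first is simpler and matches the word cessation. The cost is wording only, with no new data. The small downside is that the smokers-only estimate applies to a smaller group. The exploratory status and the low-power remark in Strengths and limitations need no change.

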#### Approval

Approval from the Danish Ethical Committee: H-4-2012-051.

Approval from the Danish Data Protection Agency referral number: 01689 RHP-2012-007.

**Table 1 10 years risk of CVD calculated with Copenhagen risk score, WC = waist circumference, BP = blood pressure, RHR = resting heart rate, HDL = high density lipoprotein, non-HDL = total cholesterol-HDL, HbA1c = glycosylated haemoglobin, FEV1 = forced expiratory volume, VO2max = maximal oxygen uptake, sedentary = hours of physical activity during leisure time spending  $\leq 1.5$  metabolic equivalents, MVPA = hours of moderate or vigorous activity**

|                    | Variables                | Expected difference, mean | Expected standard deviation | $\alpha$ | Power % |
|--------------------|--------------------------|---------------------------|-----------------------------|----------|---------|
| Primary outcome    | 10 years risk of CVD (%) | 2.5                       | 5.9                         | 0.0166   | 0.90    |
| Secondary outcomes | WC (cm)                  | 5                         | 14                          | 0.0166   | 0.75    |
|                    | BP (mm Hg)               | 5                         | 12                          | 0.0166   | 0.88    |
|                    | RHR (per minutes)        | 10                        | 20                          | 0.0166   | 0.97    |
|                    | HDL (mmol/l)             | 0.2                       | 0.4                         | 0.0166   | 0.97    |
|                    | Non-HDL (mmol/l)         | 0.45                      | 1.1                         | 0.0166   | 0.87    |
|                    | HbA1c (mmol/mol)         | 0.5                       | 1.1                         | 0.0166   | 0.94    |
|                    | FEV1 (L)                 | -0.36                     | 0.92                        | 0.0166   | 0.84    |
|                    | VO 2max       | 3.5                       | 9                           | 0.0166   | 0.73    |
|                    | Sedentary (minutes/day)  | 60                        | 140                         | 0.0166   | 0.90    |
|                    | MVPA (Minutes/day)       | 20                        | 40                          | 0.0166   | 0.97    |

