### Secondary outcomes

Cardiorespiratory fitness was originally defined as an exploratory outcome, due to insecurity of the acceptability and feasibility of the test procedure among the recruited patients. After completed data collection at baseline, we found an acceptable level of satisfying tests, and redefined fitness to a key secondary outcome. The patient's maximal oxygen uptake ( $V \cdot O_{2\max}$ ) ml oxygen/kg/min was measured using a bicycle cardiopulmonary exercise test. The test was based on L. B. Andersens cycle exercise protocol where the initial 5 min of the cycle test (Monark) the workload is 75 W for women, and 100 W for men (L. B. [48]). Then the workload is increased by 25 W/2 min till exhaustion. All patients were continuously verbally encouraged. The maximum pulse at  $VO_{2\max}$  was recorded. Forced expiratory volume (FEV1) measured with Easyone® spirometer.

Physical Activity Scale was used to determine time spent on moderate and vigorous and sedentary activity a day [49]. Waist circumference measured between the crista iliac and lowest rib, blood pressure measured on the right upper arm after 10 minutes of rest in a sitting position - the average of the two last consecutive measurements will be reported, resting heart rate after 10 minutes of rest, HDL, non-HDL-cholesterol and HbA1c.

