### Statistical analyses

#### Sample size

We expect the experimental interventions to reduce the Copenhagen risk score during 12 months from baseline by 2.5% 10-year risk for coronary heart disease in patients allocated to lifestyle coaching compared with the score in patients allocated to care coordination alone, and a similar reduction of 2.5% in care coordination compared to treatment as usual as presented in Table 1. We plan to compare all three groups and accordingly we reduced our alpha level to  $0.05/3 = 0.0166$  [65]. Allowing a power of 90% we need to recruit 150 patients to each intervention group for a total of 450 patients. This calculation is based on an SD of 5.9% of the Copenhagen risk score as found in the Inter99-investigation [38].

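### Table 1 states 0.73 power for VO2max, the key secondary outcome, but the row's own inputs with 150 per arm give 0.83

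*Protocol*

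**What the plan says.** The Sample size section derives the trial's size from the primary outcome and concludes that "we need to recruit 150 patients to each intervention group for a total of 450 patients". Because three groups are compared pairwise, alpha is divided by three: "We plan to compare all three groups and accordingly we reduced our alpha level to" 0.0166. The Data analysis section adds: "All tests will be two-tailed and unless otherwise mentioned the alpha level will be set at 0.01666". Allocation is equal ("Patients were randomized with a 1:1:1 ratio").

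Table 1 then lists, for the primary outcome and ten secondary outcomes, an expected difference, an expected SD, alpha and power. It has no column for the number of patients. The VO2max row reads "VO 2max | 3.5 | 9 | 0.0166 | 0.73". The neighbouring FEV1 row has a difference of -0.36, an SD of 0.92 and a power of 0.84. The waist circumference row has 5, 14 and 0.75.

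The Secondary outcomes section explains that fitness began as an exploratory outcome because it was unclear whether patients could and would do the test. After baseline data collection the investigators "redefined fitness to a key secondary outcome". The Outcomes part of the Discussion repeats this.

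**The concern.** At a fixed alpha and a fixed number per arm, the power of a two-group comparison of means depends only on the ratio of difference to SD and rises with it. VO2max breaks this ordering: its ratio is larger than that of waist circumference, yet its listed power is lower. It also falls 11 points below FEV1, although the two ratios differ by only 0.002.

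The row matters more than most because fitness is the one secondary outcome singled out as key. A reader who meets a null fitness result will look at the planned power to judge it. The row leaves open whether 0.73 is a misprint, whether the SD or difference is wrong, or whether fewer usable tests were assumed without saying so. The last would mean a planned loss of about one fifth of the tests, which is a different message from a typing error.

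**Working it through.** **Inputs.** 150 per arm (Sample size); alpha 0.0166 (Sample size and Table 1); two-sided test (Data analysis); differences and SDs from Table 1.

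**Formula.** With d = |difference|/SD and n per arm, the noncentrality is d × √(n/2). In the normal approximation, power = Φ(d√(n/2) − z), with z = 2.395 for a two-sided alpha of 0.0166. The exact figure uses the noncentral t with 2n − 2 = 298 degrees of freedom. At n = 150, √(n/2) = √75 = 8.660.

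**The plan's own primary figure first.** d = 2.5/5.9 = 0.424, resting on the stated SD ("This calculation is based on an SD of 5.9% of the Copenhagen risk score"). The normal approximation gives 0.899 and the t-test 0.896, against 0.90 stated. The required number is 151 per arm by the normal approximation. The planning figure therefore reproduces.

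**All eleven rows, 150 per arm, two-sided 0.0166:**

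| Outcome | d | Power (t) | Stated |
|---|---|---|---|
| 10-year CVD risk | 0.424 | 0.896 | 0.90 |
| Waist circumference | 0.357 | 0.753 | 0.75 |
| Blood pressure | 0.417 | 0.884 | 0.88 |
| Resting heart rate | 0.500 | 0.972 | 0.97 |
| HDL | 0.500 | 0.972 | 0.97 |
| Non-HDL | 0.409 | 0.871 | 0.87 |
| HbA1c | 0.455 | 0.936 | 0.94 |
| FEV1 | 0.391 | 0.836 | 0.84 |
| **VO2max** | **0.389** | **0.831** | **0.73** |
| Sedentary time | 0.429 | 0.903 | 0.90 |
| MVPA | 0.500 | 0.972 | 0.97 |

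Ten rows round exactly to the printed value. This confirms that the table was built with a two-sided t-test at 150 per arm. VO2max is the only failure.

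**VO2max by hand.** d = 3.5/9 = 0.3889. Noncentrality = 0.3889 × 8.660 = 3.368. Then 3.368 − 2.395 = 0.972, and Φ(0.972) = 0.835 (t-test 0.831).

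**Could another convention give 0.73?** Normal approximation, 150 per arm: one-sided 0.892; alpha 0.05, 0.920; alpha 0.01, 0.786; alpha 0.05/6, 0.767. None does.

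**What would give 0.73, changing one input at a time (t-test):**
- 121 per arm instead of 150: 0.729. That is 121/150 = 81% of the arm.
- SD of 10 instead of 9: 0.733.
- Difference of 3.14 instead of 3.5: 0.730.

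The Protocol states none of these.

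**The case against.** The best defence is that 0.73 may be deliberate. Table 1 has no column for n, and 150 is the number to recruit, not the number expected to complete a maximal cycle test. The Secondary outcomes section voices doubt about feasibility and speaks only of an acceptable level of satisfactory tests, so not every patient may have given one. About 121 tests per arm would produce the printed figure. Replacing 0.73 with 0.83 could then swap a realistic number for an optimistic one. This stands as a reason not to prescribe 0.83. It does not rescue the row, because no reduced number is stated for any outcome and the other ten rows all use 150.

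The second defence is that little depends on the figure. The sample size rests on the primary outcome alone, secondary results are read by bands of p-values, and the Strengths and limitations section already concedes low power for some secondary outcomes. This also stands and limits the weight of the point.

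A reader might go further and call the HbA1c row wrong too. It reads "HbA1c (mmol/mol) | 0.5 | 1.1 | 0.0166 | 0.94", and those values look like percent-scale figures: assuming about 10.9 mmol/mol per percentage point, 0.5 and 1.1 would be about 5.5 and 12 mmol/mol. The Protocol does not support that conclusion. It never gives HbA1c in percent and offers neither a conversion nor a source for the two values. The listed 0.94 follows from them, and a change of unit would leave it unchanged because the ratio 0.5/1.1 has no unit. It is a question for the authors, not a shown error.

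**Conclusion.** One row of Table 1 is wrong as written. From a difference of 3.5, an SD of 9, alpha 0.0166 and 150 per arm, the power for VO2max is 0.83; the table states 0.73, 10 points lower. The result rests on a two-sided two-sample comparison with equal arms, the settings that reproduce every other row. The internal conflict with waist circumference and FEV1 needs only that all rows share one n.

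The cause cannot be settled from the Protocol: the power, the SD, the difference or an unstated number of usable tests could each be at fault. Nor may a reader infer that the trial is under-powered for fitness or wrongly sized. With the printed inputs the error runs the other way. It is a small correction, worth making because it concerns the outcome named as key secondary.

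**What to change.** Reconcile the VO2max row against the original calculation.
- If the printed difference, SD and 150 per arm hold, restate the power as 0.83.
- If 0.73 was intended, print the input behind it: about 121 evaluable tests per arm, an SD of about 10, or a difference of about 3.14. If it was the number of tests, add a note to the table giving the n for that row and the reason.

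In the same pass, confirm the unit of the HbA1c difference and SD. The power of 0.94 stays as it is either way.

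The cost is one corrected table row and one query. The design, recruitment, alpha and analysis do not change.
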